### Trial design

The FABO-study is a randomized clinical trial (RCT) using a wait-list control design in which all recruited families of children with severe obesity will receive FBSFT at some point. All families go through initial assessments at the Obesity Outpatient Clinic (OOC) at Haukeland University Hospital, and can choose to give informed consent to participate. If informed consent is given, the families are randomized to either FBSFT (arm A) or TAU followed by FBSFT one year later (arm B). The overall study design is summarized in Fig. 1. Flow sheet for the FABO-study.

**Fig. 1 Fig1:**
[figure not shown]
Flow sheet for the FABO-study

### Blinding

The data manager and statisticians are blinded to group allocation until analyses are conducted. Blinding of participants and/or the treatment team was not possible due to the nature of the study.

### Inclusion criteria

The sample will consist of 120 children and adolescents (aged 6–18 years) referred to the OOC by their general practitioner. Criteria for admission to the clinic is an International Obesity Task Force (IOTF) BMI ≥ 35, or ≥ 30 [41] with obesity related co-morbidity. The child/adolescent participates in the treatment together with her/his family, such that both the child and a least one of the parents agree to actively participate in the treatment.

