## Background

There has been a global increase in the prevalence and severity of overweight and obesity amongst both adults and children [1, 2]. The World Health Organization (WHO) states that childhood obesity is one of the most serious public health challenges of the 21st century [2].

Childhood obesity is associated with a wide array of negative health consequences such as psychosocial problems, obstructive sleep apnea, increased cardio-metabolic risk and Type 2 Diabetes [3–5], resulting in considerable burden for the individual child as well as socio-economic consequences [6, 7]. In addition, childhood obesity has great impact on adulthood, and is associated with adult obesity [8] and all-cause mortality in adulthood [9]. A recent study [9] with 2.3 million participants between the ages of 16 and 19 years found that a graded increased risk for cardiovascular and all-cause mortality during 40 years of follow-up started among participants with a body mass index (BMI; kg/m^2^) currently accepted within the normal range (from 50th to 74th percentiles).

The need for developing potent treatments for childhood obesity has been recognized for decades and a substantial body of treatment research exists [10–12]. There is also substantial evidence indicating that it is difficult to get more than modest weight loss when treating adolescents with severe obesity [13, 14].

Several reviews and meta-analyses have summarized the results of different childhood obesity treatments and provided recommendations as to which treatments are the most efficacious and which treatment components are predictive of favorable treatment outcomes [11, 12, 15, 16]. Specifically, lifestyle interventions that teach behavioral techniques that focus on incorporating the behavior changes into daily life routines, and are delivered in a family-based format (i.e., targeting both the child and parent), seem to be the most efficacious treatment for childhood obesity [11, 15–18]. However, it is important to note that much of this research has been conducted within efficacy trials. Thus, effectiveness trials, which focus on the applicability and validity of the treatment in usual health care settings with a less selected group of participants, are warranted, as few have been conducted [19].

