### Study objectives and hypotheses

The objectives and hypotheses of the current study are:To evaluate the effect of FBSFT compared to TAU for severe childhood and adolescent obesity in a common health care setting. The primary outcome is weight status, assessed as BMI, BMI standard deviation scores (SDSs) and percentages above the IOTF cut-off for overweight (%IOTF-25) [41]. Secondary outcomes are other weight-related anthropometric measurements (waist circumference (WC) and Waist-to-height ratio (WHtR) and corresponding SDSs), body composition (BIA, DXA), blood test, blood pressure, eating habits, sleep, physical activity as well as psychological well-being and parenting style.○ We hypothesized that FBSFT will be superior to TAU in improving these parameters both during the intensive treatment period and during the follow-up period.
To identify predictors of treatment success and treatment drop out with a focus on family variables, socioeconomic status, social network and mental health.○ We expect children from families in which both parents participate in treatment to demonstrate better weight loss outcome and have lower dropout rate.○ We expect children of parents living together to demonstrate better treatment effects and have lower dropout rate.○ We expect that parental (self-reported) weight status will influence treatment effects and dropout rate; higher BMI category will predict poorer treatment effects and higher dropout rate.○ We expect that lower socio-economic status and limited social network will predict poorer treatment effects and higher dropout rate.○ We expect poorer treatment effect and higher dropout rate among participants with psychological comorbidities.
To evaluate experienced barriers to treatment, and how these factors influence children’s and parents treatment response. Barriers to treatment are classified into four groups: competing activities/life stressors, relevance of treatment, treatment issues (logistics) and critical events.○ We expect lower degree of competing activities/life stressors to predict better treatment response and lower dropout rate.○ We expect higher degree of experienced treatment relevance to predict better treatment response and lower dropout rate.○ We expect lower degree of treatment issues and lower number of critical events to predict better treatment response and lower dropout rate.

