### Exclusion criteria

Families are excluded if either the children or parents experience severe somatic or psychiatric illness that affect weight or adherence to the treatment program, or current participation in other obesity treatment programs.

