## Planned data analysis

A two-way MANOVA with one repeated-measure factor (Time: pre-intervention/post-intervention), and one between-group factor (Treatment Group: FBSFT vs. TAU) will be conducted to assess the impact of treatment on primary and secondary outcomes.

A one way within-subjects MANOVA will be used to analyze the effect of time (pre-treatment, post-treatment, 12-, 18-, 24 months post treatment) on primary and secondary outcomes.

In order to identify factors associated with treatment success and treatment drop out, multiple regression analyses will be conducted. The dependent variables are %IOTF-25 and drop-out status (yes/no). The predictors are: both parents participating in treatment, parental marital status, self-reported parental weight, socio-economic status and social network, psychological comorbidities.

In order to identify barriers to treatment and how these barriers influence children’s and parents’ treatment response, multiple regression analyses will be conducted. The dependent variable is %IOTF-25. The predictors are: competing activities/life stressors, relevance of treatment, treatment issues (logistics) and critical events.

Intention-to-treat analyses will be conducted and effect sizes calculated for treatment effects.

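### The predictor regression takes %IOTF-25 as a level and omits entry weight, although the entry rule can tie co-morbidity to entry weight, so the psychological-comorbidity coefficient can be off by several points in either direction

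*Protocol article*

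**What the plan says.** Inclusion criteria (Protocol article): the child must have an IOTF BMI of at least 35, or of at least 30 "with obesity related co-morbidity". The article does not list which conditions qualify. The Background counts "psychosocial problems, obstructive sleep apnea, increased cardio-metabolic risk and Type 2 Diabetes" among the consequences of childhood obesity, so psychological problems might qualify, but no passage says that they do. The Exclusion criteria separately remove families with "severe somatic or psychiatric illness that affect weight or adherence to the treatment program".

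Study objectives and hypotheses: "We expect poorer treatment effect and higher dropout rate among participants with psychological comorbidities".

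Planned data analysis: "The dependent variables are %IOTF-25 and drop-out status (yes/no"). The stated predictors are participation of both parents, parental marital status, self-reported parental weight, "socio-economic status and social network, psychological comorbidities". Neither the child's entry weight nor somatic co-morbidity is on the list. Anthropometrical measures defines %IOTF-25 as 100 × BMI / IOTF 25, which is a level and not a change. The Background names the child's initial weight status as a factor linked to weight-loss outcome in earlier research.

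**The concern.** A regression of follow-up level on a predictor, without the starting level, estimates

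coefficient = (slope of follow-up on entry level) × (entry gap between children with and without the predictor) + (difference in response).

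Only the last term concerns the hypothesis. The entry rule gives a specific reason to expect a non-zero entry gap. Every child without a qualifying co-morbidity is at IOTF ≥ 35, and every child at 30–35 has one. If psychological co-morbidity is tied to qualifying status or to BMI, its coefficient carries a starting-weight difference that is not treatment response. A pre-stated hypothesis of the second objective could then be supported or contradicted by who was admitted. Because the article states the predictor list, this is a matter of what is written and not of detail left out.

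**Working it through.** **The plan's own figure.** Sample size gives 55 for testing one of five predictors. With λ = f²N, df 1 and N − 6, alpha 0.05: λ = 0.15 × 55 = 8.25, df 1 and 49, power 0.804. The figure reproduces if 0.15 is read as f². (The text labels it f, which would need 351; that is a separate matter.) The calculation does not address selection at entry.

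**Inputs for the check.** From the article: the entry rule, N = 120, the definition of %IOTF-25 and the predictor list. Assumed, because the article does not give them: the share of referrals at IOTF 30–35, the co-morbidity rates, an exponential excess of IOTF-equivalent BMI over 30, and 4 %IOTF-25 points per BMI unit (100/25).

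**One case by hand.** Take 100 referrals, half at 30–35. Psychological and somatic co-morbidity are 30% each, independent of each other and of BMI, and both qualify.

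| | Psychological | No psychological |
|---|---|---|
| Referred, 30–35 | 15 | 35 |
| Admitted, 30–35 | 15 | 35 × 0.30 = 10.5 |
| Admitted, ≥ 35 | 15 | 35 |
| Share of admitted at 30–35 | 15/30 = 50.0% | 10.5/45.5 = 23.1% |

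Half below 35 means an exponential mean of 5/ln 2 = 7.21. Mean excess is 7.21 − 5 = 2.21 at 30–35 and 5 + 7.21 = 12.21 above, a difference of 10 BMI units or 40 points. Entry gap: −(0.500 − 0.231) × 40 = −10.8 points. With an assumed somatic effect of +2 points, and somatic rates of 30% versus 21/45.5 = 46.2%, a further −0.3 is added, giving −11.1. Simulation gives −11.09, with a 50% chance of a significant result at N = 120 although the true psychological effect is zero. Adding baseline %IOTF-25 gives −0.38; adding somatic co-morbidity as well gives 0.02.

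**Range if psychological problems qualify** (30–70% of referrals at 30–35, psychological 15–30%, somatic 20–60%, all independent): coefficient −3.8 to −14.6 points and false-positive chance about 9% to 83%. With baseline in the model the coefficient is −0.15 to −0.74; with change as outcome, −0.12 to −0.56; with baseline and somatic co-morbidity, about 0. The largest value belongs to the 30% share, where %IOTF-25 has a very wide SD of about 57. At the 70% share (SD 18.5 to 19.9) the range is −3.8 to −11.4.

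**If only somatic conditions qualify.** Independent of psychological problems: coefficient about 0, false positives 5%. Positively related (risk difference 0.3): −6.0.

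**If co-morbidity rises with BMI.** With 30% of each and odds rising about 10% per BMI unit, the entry gap shrinks from −7.9 to roughly −1.5 (mean excess 4), or turns from −10.1 to roughly +3.6 (mean excess 6). A rerun moved these last two values by less than one point and kept their signs. Over a wider set of such patterns the level coefficient with no true effect ran from about −12 to +15. Adding baseline %IOTF-25 removed the starting-weight error in every case.

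**What baseline alone leaves.** Within IOTF 30–35, a child without psychological co-morbidity must have another qualifying one, so the two are negatively correlated there (−0.53 to −0.83). In the whole sample the correlation is −0.06 to −0.29, and it becomes +0.16 if the two are positively related at referral. With a true effect of 3 points, the baseline-adjusted coefficient was about 1.9 to 4.0; adding other co-morbidity returned 3.0.

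**The case against.** The strongest reply is that treatment success implies change or a baseline-adjusted outcome, and that a condensed article leaves this to the full protocol or analysis plan. On that reading little is left. With an assumed residual SD of 8 and 30% prevalence, the standard error at N = 120 is 8/√(120 × 0.3 × 0.7) = 1.6, and the remaining artefact of 0.12 to 0.74 points is under half of it. This stands as a limit on the size. It does not remove the point, because the article names the dependent variable, defines it as a level and states the predictors.

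Second, the article does not say that psychological problems qualify. This stands too: if they do not, and are unrelated both to qualifying conditions and to BMI, there is no bias.

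Third, for pure prediction among this clinic's patients the association is not wrong. That is fair, but the hypothesis is worded as poorer treatment effect, and the level coefficient does not isolate that.

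**Conclusion.** The point holds in a conditional form. As written, the %IOTF-25 regression mixes entry weight with response, and the entry rule makes an entry-weight difference by co-morbidity plausible. The error can reach several %IOTF-25 points if psychological problems qualify for entry, or are correlated with qualifying conditions or with BMI. All sizes rest on assumed referral patterns.

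A reader might infer more than the article supports:
- *That the rule certainly biases this predictor.* This needs one of the conditions above, none of which is stated.
- *That children with psychological co-morbidity are lighter, so a real adverse effect would be hidden or reported as favourable.* The sign reverses if co-morbidity rises strongly enough with BMI.
- *That psychological co-morbidity goes with absence of other co-morbidity.* This is forced only within IOTF 30–35 and need not hold in the whole sample.
- *That the drop-out regression is biased.* Neither size nor direction was worked out.
- *That the trial's main result is at risk.* The randomised FBSFT versus TAU comparison is unaffected.

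**What to change.** In the %IOTF-25 predictor regression, include baseline %IOTF-25 (IOTF level at entry) as a covariate, and add an indicator for other, non-psychological obesity related co-morbidity. Use the same two covariates in the drop-out model as a precaution. A repeat of the psychological-comorbidity test in children at IOTF ≥ 35, where admission did not depend on co-morbidity, can be listed as an optional sensitivity analysis; it will have low power. The entry rule itself need not change.

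Cost: analysis wording and one or two degrees of freedom. Counting the six listed predictors as one term each, the residual degrees of freedom at N = 120 go from 113 to 111. Baseline %IOTF-25 is already measured, and co-morbidity at entry should be known from the admission assessment.

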### Exclusion criteria

Families are excluded if either the children or parents experience severe somatic or psychiatric illness that affect weight or adherence to the treatment program, or current participation in other obesity treatment programs.

### Strategies to improve adherence to intervention protocol

A standardized checklist for data collection for each child/adolescent participating in the study is created after randomization. Once per month the checklists are reviewed, and participants with missing data are reminded by either text message or phone call to complete the assessments. In the intensive treatment phase of FBSFT, sessions are rescheduled so that each family receives the same content, while delivering the sessions within a 6 month period. Sessions are rescheduled within the week when possible, and are combined with the next session or delivered by phone if the family is unable to attend (e.g., due to weather or driving conditions, scheduling conflicts). Health care workers meet weekly for on-site supervision of intervention delivery, and monthly for Skype supervision with the research team in St.Louis, MO, USA and Pittsburgh, PA, USA.

### Sample size

One hundred twenty families will be recruited, with 60 families in each treatment arm. Power estimates were calculated using G*Power, version 3.1.3. [42, 43] With two treatment groups (TAU, FBSFT), 3 measurement points (pre-treatment, 6 months post-treatment and 12 month post-treatment) and a correlation of 0.5 between the measurement points, alpha .05, power .80, a small (*f* = 0.10), moderate (*f* = 0, 25) and high (*f* = 0.40) effect size would demand respectively sample sizes of 164, 28 and 12 participants to detect a significant group X time interaction on the primary outcome. For regression analysis of predictors of treatment outcome, a small to moderate effect size is expected (*f* = 0.15), and when testing the increase in R^2^ by adding 1 predictor to an analysis including 5 predictors in total, a sample size of 55 persons will be needed.

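### The sample sizes 164, 28 and 12 are for a three-visit group-by-time test, but the planned between-arm analysis has only two time levels, so the stated power belongs to a test the plan does not run

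*Protocol article*

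**What the plan says.** **The test that was powered.** The Sample size section sets recruitment at 120 families, 60 per arm. Its inputs are two groups, "3 measurement points (pre-treatment, 6 months post-treatment and 12 month post-treatment) and a correlation of 0.5 between the measurement points", "alpha .05, power .80" and "a small (*f* = 0.10), moderate (*f* = 0, 25) and high (*f* = 0.40) effect size". It reports "sample sizes of 164, 28 and 12 participants to detect a significant group X time interaction on the primary outcome". It does not say which of the three effect sizes the 120 rests on.

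**The test that is planned.** Planned data analysis assesses the impact of treatment with a two-way MANOVA that has "one repeated-measure factor (Time: pre-intervention/post-intervention), and one between-group factor (Treatment Group: FBSFT vs. TAU"). This is the only planned analysis that compares the arms over time. A second, one-way within-subjects MANOVA covers five time points, including 12 months, and has no group factor.

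**Related text.** Outcome measures places the post-treatment visit 6 months after the pre-treatment visit. Study objectives and hypotheses expects FBSFT to be superior in the intensive phase and also in follow-up. Under Intervention, TAU lasts 12 months; under Trial design, arm B then moves to FBSFT.

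**The concern.** A group-by-time interaction over three visits has two numerator degrees of freedom and uses the 12-month data. A pre/post interaction has one and ignores them. The two tests answer different questions and need different numbers.

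Two things are at stake. First, 80% power is claimed for a test that the analysis section does not contain, so the reader does not know what power the planned comparison has. Second, the reader cannot tell whether the between-arm comparison is meant to stop at 6 months or run to 12. Twelve months is the last visit at which arm B has had TAU alone.

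**Working it through.** **Inputs, from Sample size:** k = 2 groups, ρ = 0.5, α = 0.05, power 0.80, f = 0.10, 0.25, 0.40, m = 3 visits. **From Planned data analysis:** m = 2. I read the three powered visits as pre-treatment, 6 months and 12 months on the clock used in Outcome measures.

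**Formula.** Noncentral F for a within-between interaction in repeated-measures ANOVA, sphericity assumed, total N rounded up to equal arms:

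- λ = f² · N · m / (1 − ρ)
- df1 = (k − 1)(m − 1), df2 = (N − k)(m − 1)

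**Step 1: reproduce the printed figures (m = 3).** For f = 0.10 and N = 164: λ = 0.01 × 164 × 3 / 0.5 = 9.84, df = 2 and 324, power 80.5%.

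**Step 2: same inputs with m = 2.** For f = 0.10 and N = 200: λ = 0.01 × 200 × 2 / 0.5 = 8.00, df = 1 and 198, power 80.4%.

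| f | N, three visits (power) | N, pre/post (power) | Pre/post power at the printed N |
|---|---|---|---|
| 0.10 | 164 (80.5%) | 200 (80.4%) | 72.1% |
| 0.25 | 28 (81.2%) | 34 (80.7%) | 72.1% |
| 0.40 | 12 (81.0%) | 16 (84.5%) | 70.5% |

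The three-visit column matches the article exactly, which identifies the calculation that was done. As a cross-check on the pre/post column, a normal-approximation comparison of mean change (difference in change 4f SD, SD of change √(2(1 − ρ)) = 1 SD) gives 198, 32 and 14. That is slightly lower, as expected without the small-sample correction.

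**Step 3: what 120 analysed families give.**

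| | Three visits | Pre/post |
|---|---|---|
| Power at f = 0.10 | 66.3% | 58.4% |
| Power at f = 0.25 and 0.40 | above 99.9% | above 99.9% |
| f detectable with 80% power | about 0.12 | about 0.13 |

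**Step 4: fix the between-arm difference instead of f.** Let dₜ be the between-arm difference in SD units at each visit, with d = 0 at baseline. For an interaction with two equal arms, f² = Σ(dₜ − d̄)² / (4m). With three visits and f = 0.10, Σ(dₜ − d̄)² = 12 × 0.01 = 0.12. For pre/post, the sum is d₆²/2, so f² = d₆²/16.

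| Pattern at 0, 6, 12 months | Σ(dₜ − d̄)² | d₆² | Pre/post f² | Pre/post N |
|---|---|---|---|---|
| 0, D, D/2 (half kept) | D²/2 | 0.24 | 0.0150 | 134 |
| 0, D, D (fully held) | 2D²/3 | 0.18 | 0.01125 | 178 |
| 0, D/2, D (linear growth) | D²/2 | 0.06 | 0.00375 | 526 |

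Against the printed 164, the pre/post requirement is lower in the first pattern and higher in the other two. The patterns are my assumptions; the article gives none.

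**The case against.** **The figures are not miscalculated.** This stands. The numbers 164, 28 and 12 are exact for their stated inputs. The fault is a mismatch between sections, not arithmetic.

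**The direction of the gap is not established.** This also stands. A reader might infer that all three printed sizes are too low for the planned analysis. That holds only if f is kept constant while the number of visits changes, and the same f is not the same treatment difference in the two designs. If half the 6-month effect is kept at 12 months, pre/post needs 134, 24 and 12 for the three effect sizes, no more than the printed 164, 28 and 12. The article's own Background calls long-term maintenance a challenge, so partial fading is plausible.

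**The recruited number hardly depends on it.** Largely true. At f = 0.25 and 0.40 the trial has ample power either way. At f = 0.10, 120 falls short of both 164 and 200.

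**There are not two primary tests.** A reader might infer that the plan holds two rival primary tests and so an inflated false-positive rate. The article labels no test primary, plans only one of the two, and nowhere says that success on either would count. An error rate built on such a rule would not describe this plan.

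**200, 34 and 16 are not fully the numbers for the planned MANOVA either.** Correct if BMI, BMI SDS and %IOTF-25 are tested jointly. That would need inputs the article does not give.

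None of this removes the mismatch. Nor is it a detail left to a fuller document: the article states both tests, and they differ.

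**Conclusion.** The concern holds as an inconsistency between Sample size and Planned data analysis. The stated 80% power belongs to a three-visit interaction that the plan does not run.

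For a single outcome at the article's own f, ρ, α and power, the pre/post test needs 200, 34 and 16, and the printed sizes give about 72%, 72% and 71% power. These figures assume constant f. For a fixed between-arm difference at the f = 0.10 level, the pre/post requirement is 134, 178 or 526 under the three patterns shown, so the documents do not support saying in which direction the printed numbers err.

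The practical effect at 120 analysed families is moderate: 66% versus 58% power at f = 0.10, and no material difference at f = 0.25 or 0.40. The article should be corrected, but the mismatch does not undermine the trial.

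**What to change.** Make the two sections describe the same test. Either route is sufficient.

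- **(a) Add the 12-month visit to the group-by-time analysis** in Planned data analysis. This keeps 164, 28 and 12 valid, fits the follow-up hypothesis, and uses the last comparison before arm B starts FBSFT. State that the repeated-measures factor is tested in the univariate form behind those numbers; the multivariate form over three visits needs 164, 30 and 14.
- **(b) Keep the pre/post test and restate Sample size** as 200, 34 and 16 for a single outcome. Add that 120 analysed families give 58% power at f = 0.10 and 80% at about f = 0.13.

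The follow-up hypothesis and the 12-month length of TAU favour (a), but the choice is the sponsor's. The cost is one reworded paragraph and no extra families. Under (b) the stated figures become less favourable.

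### The sample sizes 164/28/12 are for a three-time-point group-by-time test, but the only planned between-group test has two time points, and the effect that 120 families should detect is not stated

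*Protocol article*

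**What the plan says.** The Sample size section sets 120 families, 60 per arm. Its power calculation, run in G*Power, uses two groups, "3 measurement points (pre-treatment, 6 months post-treatment and 12 month post-treatment) and a correlation of 0.5 between the measurement points", alpha .05 and power .80. It considers "a small (*f* = 0.10), moderate (*f* = 0, 25) and high (*f* = 0.40) effect size" and concludes that these "would demand respectively sample sizes of 164, 28 and 12 participants to detect a significant group X time interaction on the primary outcome". It does not say which of the three effects the 120 families are meant to detect.

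The Planned data analysis section assesses the impact of treatment on primary and secondary outcomes with a two-way MANOVA. This has a treatment-group factor and "one repeated-measure factor (Time: pre-intervention/post-intervention"). A second, one-way within-subjects MANOVA covers pre-treatment, post-treatment and 12, 18 and 24 months, but has no group factor.

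The Outcome measures section defines post-treatment as 6 months from pre-treatment. I therefore read the three points in the power calculation as 0, 6 and 12 months.

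**The concern.** The test that was powered and the test that is planned have different numbers of time points. In a repeated-measures interaction test, that number enters both the noncentrality parameter and the degrees of freedom, so the required sample size changes with it. No analysis in the plan compares the arms over three time points, so the stated sizes describe a test that the trial is not committed to run.

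The missing target effect adds to this. The number 120 lies below the 164 given for a small effect and far above the 28 and 12 given for the others, so none of the three scenarios explains it. A reader cannot tell from the article what difference between arms the trial could reliably find, and needs to know that to interpret a non-significant result.

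**Working it through.** **Inputs, all from the Sample size section except the last.** Groups k = 2; correlation rho = 0.5; alpha = 0.05; power = 0.80; f = 0.10, 0.25 and 0.40; N = 120. The number of time points m is 3 in Sample size and 2 in Planned data analysis.

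**Formula.** This is the G*Power calculation for a within-between interaction with sphericity. Power is the upper tail of a noncentral F with
- lambda = f² × N × m / (1 − rho)
- df1 = (k − 1)(m − 1) and df2 = (N − k)(m − 1)

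The required N is the smallest even total with power of at least 0.80.

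**Step 1: reproduce the stated figures (m = 3).**
- f = 0.10, N = 164: lambda = 0.01 × 164 × 3 / 0.5 = 9.84; df 2 and 324; power 0.805.
- f = 0.25, N = 28: lambda = 0.0625 × 28 × 3 / 0.5 = 10.5; df 2 and 52; power 0.812.
- f = 0.40, N = 12: lambda = 0.16 × 12 × 3 / 0.5 = 11.52; df 2 and 20; power 0.810.

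This gives 164/28/12 exactly. Other forms of the calculation with three points do not give all three figures: the multivariate form of the interaction test gives 164/30/14, the between-group main effect 526/86/36, and lambda without the correlation term 484/80/32.

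**Step 2: change only m, from 3 to 2.**
- f = 0.10: N = 200; lambda = 0.01 × 200 × 2 / 0.5 = 8.0; df 1 and 198; power 0.804.
- f = 0.25: N = 34; lambda = 0.0625 × 34 × 2 / 0.5 = 8.5; df 1 and 32; power 0.807.
- f = 0.40: N = 16; lambda = 0.16 × 16 × 2 / 0.5 = 10.24; df 1 and 14; power 0.845.

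At the stated 164, 28 and 12, the two-point test has power 0.721, 0.721 and 0.705.

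**Step 3: what 120 families deliver.**

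| Quantity, N = 120, rho = 0.5 | 3 time points | 2 time points |
|---|---|---|
| lambda at f = 0.10 | 7.2 | 4.8 |
| Power at f = 0.10 | 66.3% | 58.4% |
| Power at f = 0.25 | above 99.9% | 99.97% |
| Smallest f with 80% power | 0.116 | 0.129 |

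A simulation of the two-point test as a t test on change scores (20,000 runs, N = 120, f = 0.10) gave 58.1%.

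**Step 4: translate f for the pre/post test.** With two arms and two times, the interaction moves each cell mean by f outcome SDs. Change therefore shifts by 2f in one arm and −2f in the other, a difference of 4f. For f = 0.129 this is 4 × 0.129 = 0.52 SD. The SD of change is SD × √(2(1 − rho)), which equals the outcome SD at rho = 0.5.

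**Step 5: sensitivity to rho (values other than 0.5 are my assumption).** For two points, N = 120 and f = 0.10, power is 58% at rho 0.5, 80% at 0.7 and 93% at 0.8. At rho 0.7, for example, lambda = 0.01 × 120 × 2 / 0.3 = 8.0.

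**The case against.** **The power calculation may be right and the analysis section wrong.** The stated hypothesis claims superiority during follow-up as well as during intensive treatment, measurements are scheduled at 6 and 12 months, and arm B starts FBSFT only after one year of TAU. A comparison of the arms at 0, 6 and 12 months fits this design well. If that is the intended analysis, 164/28/12 stand and the sizes 200/34/16 are not needed. This objection stands: the documents show that the two sections disagree but do not show which one to correct.

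**The mismatch changes little in practice.** The article prints 164 beside 120, so the shortfall for a small effect is already visible. Power there is 66% even with three points, and the mismatch costs about 8 further points (66.3 − 58.4 = 7.9). Under either design 120 is below the size for f = 0.10 and ample for f = 0.25 and above. This also stands, and it limits the severity.

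**Stronger readings that the documents do not support.** A reader might infer an arithmetic error; there is none, since the stated sizes follow exactly from the stated inputs. A reader might call the trial underpowered because 120 gives 58% power, but the protocol never claims to target f = 0.10, and the figure depends strongly on rho. A reader might also treat the Background remark that "it is difficult to get more than modest weight loss when treating adolescents with severe obesity" as showing that the expected effect is small. That remark concerns weight loss in adolescents, not a difference between arms, and nothing maps it to a value of f. Finally, an allowance for dropout is a detail that an article may leave to the full protocol, and any rate chosen here would be the reader's own.

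**Conclusion.** The inconsistency is real and should be fixed. The sample sizes refer to a three-point group-by-time test, and the plan contains only a two-point one. Applied to the planned test, the stated sizes give 71% to 72% power rather than 80%; restoring 80% takes 200/34/16. Separately, the effect that 120 families are meant to detect is not stated. At 80% power it is f = 0.116 with three points or f = 0.129 with two.

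These results keep the protocol's own alpha and rho = 0.5, assume 120 families analysed, and treat one outcome at a time. Sphericity is also assumed for the three-point case. A MANOVA taken jointly over several outcomes would need a different calculation.

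The point concerns stated figures. It shows neither that 120 is too few nor that the pre/post test is the wrong analysis.

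**What to change.** Choose one of two routes and make both sections agree. Enrolment stays at 120.

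- **(a) Extend the analysis.** Make the between-group analysis a group-by-time test over 0, 6 and 12 months. Keep 164/28/12, and add that 120 analysed families give 80% power for f = 0.116. If the multivariate form of the test is used, 28 and 12 become 30 and 14.
- **(b) Restate the sizes.** Keep the pre/post test, replace 164/28/12 by 200/34/16, and add that 120 analysed families give 80% power for f = 0.129, a difference in change of about 0.52 SD at rho = 0.5.

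Route (a) costs slightly more analysis, on visits already scheduled. Route (b) costs a less favourable stated figure. Neither affects randomisation, visits or data collection.
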